### Outcome

The primary outcome of this study is correct antisaccade latency, measured at baseline, post-1- and post-2-assessment in the antisaccade task. The secondary outcome is antisaccade error rate, also measured at baseline, post-1- and post-2-assessment in an antisaccade task.

Psychophysiological measures include startle response, heart rate, and skin conductance level, measured at baseline and post-2-assessment in a free-viewing task. As a behavioral measure of avoidance, the final distance in the behavioral avoidance test (BAT) is conducted at baseline, post-1- and post-2-assessment. For psychometric assessment, the SPQ is obtained at baseline and post-2-assessment.

To characterize the sample, we additionally obtain a range of self-report measures, described in Fig 1. All self-assessment questionnaires are given out in the German version.

### Analysis

#### Preprocessing

*Eye tracking*. To detect saccadic eye movements, conservative thresholds are used. Saccades are defined as eye movements with a velocity > 35°/sec, an acceleration > 9500°/sec^2^ and an amplitude > 3°. For the trial to be classified as valid, onset latency of the first saccadic eye movement after stimulus onset must be greater than 70 ms. Starting coordinates of the eye movement must fall within a square of 5° x 5° around the fixation stimulus. Additionally, blinks must be absent. Trials with no recorded eye movements after stimulus onset are also classified as invalid. A correct antisaccade (secondary outcome) is defined as a valid saccade in the opposite direction of the peripheral visual stimulus. Antisaccade latency (primary outcome) is defined as the time difference between stimulus onset and initiation of the correct antisaccade. Participants are excluded from analysis if > 50% of maximal possible trials are invalid.

*Psychophysiological data*. ECG data is pre-processed using the PhysioData Toolbox (Version 0.6.3) [49]. The signal is filtered using a bandpass filter with a low cut-off at 1 Hz and a high cut-off at 50 Hz. From the ECG signal, R-peaks are retrieved, which serve to calculate heart rate measures. The ECG signal are visually inspected for artifacts, as well as erroneous or missed R-peaks. Missed R-peaks are added manually, erroneous R-peaks are deleted. Trials with artifacts in the ECG signal are discarded.

Skin conductance data is pre-processed using the PhysioData Toolbox. The raw signal is filtered and resampled to a 20 Hz time-vector spanning the length of the filtered signal, using spline interpolation. By first applying a moving minimum filter, followed by smoothing the result applying a Gaussian kernel, the tonic component is calculated. The phasic component is calculated by applying a 1st order high pass Butterworth filter of 0.5 Hz. The signal is visually inspected for artifacts. Trials with artifacts in the SCL signal are discarded.

The raw EMG signal is filtered using a band-pass filter ranging from 10 to 500 Hz, as well as rectified and smoothed, using a low-pass resistor-capacitor filter, utilizing a time constant of 10 ms. A C++-based software tool is used to identify peak responses in the rectified and integrated EMG signal. Additionally, the signal is visually inspected for artifacts (e.g., preceding blinks immediately before the startle probe), as well as erroneously detected response peaks. Trials with artifacts in the EMG signal are discarded, erroneously detected response peaks are corrected manually. Startle response amplitude is defined as the difference between EMG peak and baseline amplitude in a 200 ms response window.

#### Statistical analyses

In the following, planned analyses will be described in brief. Further details on statistical analyses for aim 1 and aim 2, can be found in the detailed statistical analyses protocols for each aim. For further details on aim 3, a statistical analyses protocols will be preregistered with Current Controlled Trials (ID: ISRCTN12918583).

Corresponding to aim 1 of the study, baseline differences in antisaccade performance between participants with SP and HCs will be investigated using general linear modeling with antisaccade latency and antisaccade error as outcome respectively. Diagnosis will be entered as a between-subject-factor, stimulus category as a within-subject factor, resulting in a 2x2 design. To investigate associations between multimodal measures of fear (psychophysiological responses, BAT and SPQ scores) and antisaccade performance in SPs, multiple regression analyses will be conducted with the primary and secondary outcome as dependent variables, respectively. If relevant demographic or psychometric measures differ between groups, these measures will be entered as covariates (for statistical analysis plan see ISRCTN12918583). Corresponding to aim 2 of the study, general linear modelling will be conducted with diagnosis and intervention (antisaccade training vs. prosaccade training) as between-subject factors, as well as time and stimulus category as within-subject factors, resulting in a 2x2x2 design, including antisaccade latency and error rate as outcomes. Again, potential confounds showing group differences will be entered as covariates (for statistical analysis plan see ISRCTN12918583).

Corresponding to aim 3 of the study, exploratory analyses will be conducted in SPs, associating changes in antisaccade performance (antisaccade latency and error rate, pre vs. post-2) with changes in physiological responses to fear-specific stimuli, avoidance behavior, and self-reported fear of spiders (baseline vs. post-2). Additionally, antisaccade latencies and error-rates will be investigated via general linear modelling with intervention (antisaccade training first vs. prosaccade training first) as between-subject factors, as well as time (baseline, post-1, post-2) and stimulus category as within-subject factors, resulting in a 2x2x3 design. BAT scores will be investigated via general linear modelling with intervention (antisaccade training first vs. prosaccade training first) as between-subject factors, and time (baseline, post-1, post-2) as within-subject factor.

For all analyses significance levels will be set to *p* = .05.

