To further elucidate the role of inhibitory control performance in specific phobia, the present study investigates antisaccade performance in patients with spider phobia (SP) compared to healthy controls (HC). As the literature on (dispositional) anxiety and inhibitory control mainly indicates inhibitory control deficits with regard to efficiency rather than effectiveness, antisaccade latency serves as the primary outcome. Antisaccade error rate (as a marker of inhibitory control effectiveness) is investigated as a secondary outcome. Our study follows three main aims: First, patients with spider phobia (as a model anxiety disorder) are investigated via the antisaccade task regarding potential inhibitory control deficits and their associations to certain stimulus materials (phobia-related versus neutral), psychophysiological (heart rate, skin conductance, startle-response), behavioral and psychometric measures of fear (aim 1). This aim employs a proof-of-concept mixed factorial design with the between subject factors group (SPs vs. HCs) and the within-subject factor stimulus material (phobia-related vs. neutral). Second, the modifiability of inhibitory control through a fear-specific antisaccade training is piloted (aim 2). This aim employs an exploratory randomized controlled parallel group design with two training conditions (antisaccade training vs. control) that is realized in SPs and HCs. Changes in antisaccade performance from baseline to post-1-assessment, and their dependence on stimulus material is assessed. Third, putative changes in inhibitory control performance following the training are investigated regarding associations to changes in psychophysiological, behavioral, and psychometric measures of fear in SPs, therefore exploring possible therapeutic utility (aim 3). This aim employs an exploratory cross-over design in SPs only, i.e. patients switch training conditions after the post-1-assessment, and are assessed regarding antisaccade performance, psychophysiological (heart rate, skin conductance, startle-response), behavioral and psychometric measures of fear at post-2-assessment.

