### Sample size

Based on two studies using the antisaccade task in clinical samples, we calculated two a-priori power analyses using G*Power 3.1 [25] for ANOVAs (Analyses of Variance) to detect large effect sizes (Cohen´s *f* = .40, *α* = .05, power = .85) in our primary outcome (i.e. antisaccade latencies) at baseline (aim 1) [12] and for the training effect (aim 2) [21]. Results indicated a required total sample size of 59 participants (30 per group).

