### Randomization and blinding

The randomization scheme was implemented utilizing block randomization. Participants are randomized via sequential numbers provided in a separate document.

Though participants are not especially informed about their allocation to a certain condition, they might have been aware of the condition. A blinding of investigators is not possible.

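### Aim 2 tests the randomised training effect on change scores and leaves baseline latency out as a covariate, which usually costs some precision

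*Protocol article*

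**What the plan says.** The protocol article, Background, describes aim 2 as follows: "This aim employs an exploratory randomized controlled parallel group design with two training conditions (antisaccade training vs. control"). It is run in patients with spider phobia (SP) and in healthy controls (HC), and it looks at change from baseline to post-1. On allocation, Randomization and blinding says: "The randomization scheme was implemented utilizing block randomization".

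Statistical analyses sets out the aim 2 model for latency and error rate. Diagnosis and training are between-subject factors, "as well as time and stimulus category as within-subject factors". The sentence on covariates reads "Again, potential confounds showing group differences will be entered as covariates" and is followed by a pointer to a registered analysis plan that is not shown here. The section describes the analyses in brief and leaves further detail for aims 1 and 2 to separate documents.

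Outcome and Overall procedure show that latency is measured at baseline, before any training, in all participants. Sample size states that a power analysis was done "in our primary outcome (i.e. antisaccade latencies) at baseline (aim 1) [12] and for the training effect (aim 2").

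**The concern.** In the stated model, baseline latency appears only as one level of the time factor. With two levels of time, the training-by-time interaction is algebraically a comparison of mean change between training arms. That fixes the weight on baseline at one, whatever the data show. When arms are randomised, the regression of post-1 on baseline is also unbiased for the training effect, and it estimates the weight that removes most noise. Unless baseline and post-1 are very highly correlated, the planned test therefore gives a wider interval than data already collected would allow.

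The covariate rule does not repair this. It enters variables because groups differ on them, not because they predict post-1 latency. It also does not say whether it extends to the two training arms. If it did, covariates for a randomised contrast would be chosen by chance imbalance.

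**Working it through.** **Inputs from the protocol article.**
- Sample size: "to detect large effect sizes (Cohen´s *f* = .40, *α* = .05, power = .85") and "Results indicated a required total sample size of 59 participants (30 per group").
- Statistical analyses: "For all analyses significance levels will be set to *p* = .05".

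**Assumptions, not in the document.**
- Correlation ρ between baseline and post-1 latency: .5 to .95.
- Equal variance at both times, and normally distributed baseline.
- 60 participants as four cells of 15 (30 SP and 30 HC, each split evenly between training arms).

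**1. The plan's own figure.** F test with 1 numerator degree of freedom and noncentrality f²N = .16N. With four cells, power is .849 at N = 58, .855 at N = 59 and .861 at N = 60. The smallest N reaching .85 is 59, so the stated sample size reproduces.

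**2. Large-sample variances,** in units of the common variance:
- Change score: 2(1 − ρ).
- ANCOVA: 1 − ρ² = (1 − ρ)(1 + ρ).
- Ratio ANCOVA/change: (1 + ρ)/2.

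**3. Cost of estimating the slope at this size.** The expected inflation of the ANCOVA variance is 1 + 1/(residual degrees of freedom without the covariate − 2).
- Common slope, 60 people in 4 cells: 1 + 1/(56 − 2) = 55/54 = 1.019.
- Slope per diagnosis, 30 people in 2 cells each: 1 + 1/(28 − 2) = 27/26 = 1.038.

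**4. Ratio at this size.**

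| ρ (assumed) | Large sample | Common slope | Slope per diagnosis |
|---|---|---|---|
| .5 | .75 | .76 | .78 |
| .7 | .85 | .87 | .88 |
| .8 | .90 | .92 | .93 |
| .9 | .95 | .97 | .99 |
| .95 | .975 | .99 | 1.01 |

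**5. Break-even.** Setting the ratio to 1:
- Slope per diagnosis: ρ = 2 × 26/27 − 1 = .926.
- Common slope: ρ = 2 × 54/55 − 1 = .964.

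**6. Simulation check.** With four cells of 15 and 20,000 replicates, the ratios for a slope per diagnosis were .778, .887, .933, .982 and 1.021 at ρ = .5, .7, .8, .9 and .95. With a common slope they were .765, .870, .916, .965 and .999. All three estimators were unbiased for the training effect.

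**7. Interval width.** Taking square roots for a slope per diagnosis, standard errors shrink by about 12%, 6%, 3% and 1% at ρ = .5, .7, .8 and .9.

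**The case against.** **The planned analysis is not wrong.** It is unbiased, it uses baseline through the change, and it matches an aim worded in terms of change. Aim 2 is also labelled exploratory. All of this stands, so the point is one of efficiency only. It still deserves action because the article runs a power analysis for this effect on the primary outcome.

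**The gain may be small.** Baseline and post-1 fall within one appointment, and each uses 60 antisaccades per stimulus category (three blocks of 20), so a high correlation cannot be ruled out. This stands too. A reader might infer that ANCOVA is never less precise than change scores. At this size that fails above about .93 with a slope per diagnosis, and above about .96 with a common slope.

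**A gain in power cannot be quoted.** A reader might convert the ratios into power at f = .40. The article does not say whether that effect is in units of the standard deviation of change or of post-1 latency, and the gain depends on which is meant and on the unknown correlation. Nor does the section state a separate test of training within patients.

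**The covariate rule may be legitimate.** A reader might infer that the plan tests the randomised arms for imbalance and adjusts for significant differences. The text does not support that. The opening word refers back to the aim 1 rule, where the only groups are SP and HC, and the Background uses group for diagnosis and condition for training. Diagnosis is not randomised, so adjusting that comparison for confounders has a rationale. No significance test is mentioned, and the detail is left to a plan not shown. What remains is that the sentence, placed after a model with both factors, does not say that the training effect is outside its scope.

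**Conclusion.** The point holds as one of precision, not validity. As stated, the aim 2 model tests the randomised training effect on change scores and does not use baseline latency as a covariate. Baseline adjustment would lower the variance of the training estimate by roughly 22% at a correlation of .5, 12% at .7, 7% at .8 and 1% at .9, with a slope per diagnosis. Above about .93 it would bring nothing.

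These sizes rest on an assumed correlation, equal variances at baseline and post-1, and about 15 participants per cell. The form of the model is on the page and does not depend on the unseen plan. That plan may add detail on covariates, so on the covariate rule the finding is limited to unclear scope.

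**What to change.** 1. For the randomised training contrast, model post-1 latency per stimulus category on training, diagnosis, training by diagnosis, and stimulus category with its interactions. Include category-specific baseline latency as a pre-specified covariate. State in advance whether its slope is common or differs by diagnosis. Do the same for error rate.
2. Keep the repeated-measures model to describe change over time and diagnosis by time, which the baseline-adjusted model does not report.
3. State that the rule on confounds applies only to the non-randomised comparison of SP with HC, and that it does not choose covariates for the training effect. The documents identify no further prognostic variable for latency, so none is proposed here.

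The cost is one slope degree of freedom (two if slopes differ by diagnosis) and one added model. No new data, visits or participants are needed.

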## Discussion

The present study is designed to compare the antisaccade performance of SPs to a HC group and to examine the putative potential of an antisaccade training with phobia-related stimuli to increase inhibitory control in specific phobia. It also aims to explore associations between antisaccade performance and multimodal psychophysiological, behavioral, and psychometric measures of fear.

Focusing on the comparison of SPs and HCs (aim 1), a decreased antisaccade performance in SPs would yield evidence for reduced inhibitory control functions in SPs. This finding would extend previous findings, which have yielded evidence for associations between antisaccade performance and subclinical anxiety levels [16, 17], to clinically anxious individuals. Thereby, such findings would provide further evidence for a key role of inhibitory control processes in the pathogenesis and maintenance of specific phobia. Such evidence from the study of antisaccade performance would complement previous evidence from the field of fear conditioning, which has suggested deficient inhibitory learning processes and reduced inhibition of fear responses to safe stimuli in patients with pathological anxiety [50] and non-responders to exposure therapy in spider phobia [51]. As spider phobia is used as a model disorder for anxiety disorders more broadly, results could also serve as foundation for research on a wider range of anxiety disorders.

To estimate the clinical relevance of putative deficits in antisaccade performance (i.e., inhibitory control), it seems pivotal to shed light to its link with symptoms of fear. We therefore investigate relationships between antisaccade performance and multimodal measures of fear (e.g., psychophysiological fear responses, avoidance behavior as assessed via the BAT, and self-reported symptoms as assessed via the SPQ). The finding of significant associations could broaden our knowledge on the mechanistic basis of specific aspects of the fear response and form the basis for future research on a potential (causal) role of inhibitory control on fear-associated symptoms.

If a lower inhibitory control is found in patients with pathological anxiety, an antisaccade training could increase antisaccade performance as seen in previous studies investigating patients with other disorders [20, 21]. Aim 2 of this study targets this hypothesis. A positive result would suggest that an antisaccade training does increase inhibitory processes, which may in turn be a factor related to treatment outcomes in specific phobia [52]. If this is the case, the generalizability of improved antisaccade performance to clinically relevant measures of fear and anxiety would be of importance. According to aim 3 of this study, we therefore investigate whether changes in antisaccade performance generalize to other measures of fear. Positive results regarding aim 2 and potentially also aim 3 would point towards the potential of the antisaccade training as a mechanism-informed targeted intervention for anxiety disorders [53]. As such, it might yield add-on effects to existing treatments and increase treatment response.

To conclude, findings of this study on patients with spider phobia (as a model for anxiety disorders more broadly) can strengthen our understanding of the mechanistic underpinnings of anxiety disorders and potentially pave the way for new targeted interventions.

## Abbreviations

ABI: an inventory of coping with anxiety
ANOVA: Analysis of Variance. ANPS: Affective Neuroscience Personality Scales
ASI-3: Anxiety Sensitivity Index
BAS: Behavioral Approach System
BAT: Behavioral Avoidance Test
BIS: Behavioral Inhibition System
CERQ: the Cognitive Emotion Regulation Questionnaire
dB: decibel
ECG: electrocardiography. EMG: electromyography. FEAS: Questionnaire on Disgust and Fear of Spiders
FEE: Disgust Responsiveness
GAPED: Geneva Affective Picture Database
HC: Healthy control participants
Hz: hertz
ITI: Inter-Trial-Interval
m: meters. MINI: Mini International Neuropsychiatric Interview
ms: milliseconds. MWT-B: Multiple-Choice Vocabulary Intelligence Test
n: number of participants
NISS: Need Inventory of Sensation Seeking
NEO-FFI: NEO Five-Factor Inventory
PANAS: Positive and Negative Affect Schedule
RSES: Rosenberg Self-Esteem Scale
s: seconds
SCID-I: Structured clinical interview for the Diagnostic and Statistical Manual of Mental Disorders-IV
SCL: Skin Conductance Level. SEE: Scales for experiencing emotions
SP: Patients with spider phobia
SPQ: Spider Phobia Questionnaire
STAI: State-Trait-Anxiety-Inventory
UI-18: Intolerance of Uncertainty Scale
